### Statistical analysis

#### Planned analysis

To assess the agreement between the MDM-C and MDM-AB recommendations, interrater reliability will be examined.

To examine the reproducibility of ADBoard decisions, intrarater reliability will be studied. A third reference MDM will be conducted externally in the event of discordance between the recommendations of MDM-AB and MDM-C. The interrater reliability between the reference MDM and MDM-AB as well as between the reference MDM and MDM-C will be determined. A Cohen’s kappa value of ≥ 0.75 (*p* < 0.05, *Z* test) is postulated for the interrater reliability for both comparisons. If there is no agreement between MDM-AB and MDM-C, the reference MDM can evaluate which conference is most likely to be guideline- and evidence-based. This arbitrarily chosen value corresponds to a “good to excellent reliability” [13]. The basis of the data analysis is the dataset collected up to T1 (time of the conventional MDM).

Oncological and patient-specific parameters, which are necessary for the therapy decision of the respective disease and are predefined for each tumor type, will be compared between the ADBoard-recommended protocol (based on the dataset collected up to T1), the MDM-C, and the reference MDM (descriptive evaluation, target value for feature expression of the ADBoard decision 100%, *p* < 0.05, Mann–Whitney *U* test). We predict an improvement in the documentation according to the legal requirements.

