The follow-up ends with the initiation of the MDM recommendation. Both study arms will be validated by an external, conventional MDM conducted at the end of the follow-up period to serve as a reference. This reference MDM will be conducted by experts in hepatobiliary tumors from the departments of surgery and oncology as soon as the recommendation has been initiated, typically within 4 weeks after conducting MDM-C and MDM-AB. It would only be conducted as part of the study. Its slightly delayed timing would ensure that any information not available at the time of the initial MDM-AB and MDM-C could be processed.

To improve adherence to the study, the research team will ensure the availability of logistics such as the designated computer enabled to run the algorithm and physician availability and presence during the MDM to carry out the intervention.

Both groups of participants would receive baseline care, that is, all cases would be evaluated at a conventional MDM. Participants retain the right to accept or refuse recommended treatments.

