### Sample size

#### Calculation of sample size

The evaluation of the primary outcome is based on Cohen’s kappa test (inter- and intrarater comparison) for nondichotomous decision-making. There are five possible recommendation categories: surgical resection or transplantation, chemo-/immunotherapy, interventional therapy, re-intervention, and further diagnosis. A five-category nominal scale will be used between different raters or different ratings of the same instance. The frequency of each category is not evenly distributed here but is estimated to be 0.3 for resection or transplantation, 0.3 for chemotherapy, 0.2 for follow-up, 0.1 for intervention, and 0.1 for further diagnosis. To capture any deviation from this estimate, different expressions of the frequencies were included in Table 1. The null hypothesis was defined as a Cohen’s kappa value of 0.7, as reliability below this value can be considered clinically unacceptable. The reliability strength to be achieved was set at 0.8 (primary endpoint: kappa value ≥ 0.75). Based on these specifications, the required numbers of cases were taken from the calculations of Bujang and Adnan [12]. A total of 3000 patients will be included in the retrospective part of the study and 1200 patients will be included in the prospective part.

**Table 1 Tab1:** Indication of the numbers of cases required for different relative frequencies of a 5-category nominal scale [12]. Number of categories: 5, type I error (*ɑ*): 0.05, null hypothesis (Cohen’s kappa): 0.7, primary endpoint (Cohen’s kappa): 0.8

Relative frequencies	Required number of cases (power 80%)	Required number of cases (power 90%)
0.3, 0.3, 0.2, 0.1, 0.1	240	311
0.3, 0.25, 0.2, 0.1, 0.05	254	329
0.6, 0.1, 0.1, 0.1, 0.1	306	400

The required numbers of cases depending on the relative frequencies of the recommendation types are displayed in Table 1.

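### The protocol gives two different rules for which cases the reference MDM reviews, and under the discordant-only rule the kappa target of 0.75 for both reference comparisons cannot be met

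*Protocol article*

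**What the plan says.** Two sections of the protocol article define the work of the reference MDM.

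- **Study design** (text after Fig. 1): "Both study arms will be validated by an external, conventional MDM conducted at the end of the follow-up period to serve as a reference". There is no restriction to cases in which the boards differ. The review takes place "as soon as the recommendation has been initiated", typically within 4 weeks. The delay is explained as a way to let in information that was not available at the first meetings.
- **Planned analysis**: "A third reference MDM will be conducted externally in the event of discordance between the recommendations of MDM-AB and MDM-C". The next sentence reads "The interrater reliability between the reference MDM and MDM-AB as well as between the reference MDM and MDM-C will be determined". A kappa of at least 0.75, with p < 0.05 by Z test, "is postulated for the interrater reliability for both comparisons". The same paragraph bases the data analysis on the dataset up to T1, the time of the conventional MDM, and lets the reference MDM judge between the boards where they differ.

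The Data collection plan adds that every case goes to MDM-C, while ADBoard processes the cases randomized to MDM-AB.

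**The concern.** The two sections define different sets of reviewed cases. The choice between them decides whether the reference comparisons can be estimated. Under the Planned analysis rule a case is reviewed because the two boards disagree, so selection depends on the very outcome being studied. Two high kappas are then expected from cases in which the reference cannot side with both boards.

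The reference MDM is the only independent standard in the document. Concordance between MDM-AB and MDM-C does not show which board is closer to that standard when they differ. A target that cannot be met on the reviewed cases would leave that question without a usable answer, or invite an analysis rule chosen after the data are seen.

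A smaller inconsistency concerns the information used. The reference MDM may draw on later information, while the analysis is tied to T1. A disagreement with the reference could then reflect new data and not a different judgement.

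**Working it through.** **Inputs**

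- Category frequencies (Calculation of sample size): "estimated to be 0.3 for resection or transplantation, 0.3 for chemotherapy, 0.2 for follow-up, 0.1 for intervention, and 0.1 for further diagnosis". With equal margins, chance agreement is pe = 0.3² + 0.3² + 0.2² + 0.1² + 0.1² = 0.24.
- Hypotheses in Table 1: "null hypothesis (Cohen’s kappa): 0.7, primary endpoint (Cohen’s kappa): 0.8", with "type I error (*ɑ*): 0.05".
- 1200 prospective patients randomized 1:1, so about 600 per arm.

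**1. The plan's own figure.** Table 1, row 1, gives 240 cases (80% power) and 311 (90% power). The formula is n = [(z(1−α/2)·τ(0.7) + z(power)·τ(0.8)) / 0.1]², where τ is the largest asymptotic standard error factor for kappa over 5×5 tables with these margins: τ(0.7) = 0.581 and τ(0.8) = 0.487.

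- 80%: [(1.96 × 0.581 + 0.842 × 0.487) / 0.1]² = 239.9, so 240.
- 90%: [(1.96 × 0.581 + 1.282 × 0.487) / 0.1]² = 310.9, so 311.

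Both match with two-sided α. One-sided α gives 187 and 250.

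**2. Discordant cases only.** Kappa = (po − pe)/(1 − pe), so po = kappa + pe(1 − kappa), which is never below kappa. In a discordant case the reference agrees with MDM-AB, with MDM-C or with neither, so po(ref,AB) + po(ref,C) ≤ 1.

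- For any pe, two kappas of 0.75 need a sum of at least 0.75 + 0.75 = 1.5. This contradicts the limit of 1.
- With pe = 0.24, each po must be 0.75 + 0.25 × 0.24 = 0.81, a sum of 1.62.
- Even split: (0.50 − 0.24)/0.76 = 0.34 in both.
- If one comparison reaches 0.75, the other has po of at most 0.19, so kappa is at most (0.19 − 0.24)/0.76 = −0.07.

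**3. Concordant cases counted as agreeing with the reference.** The document does not state this rule; it is tested here as an assumption. Let k be the kappa of MDM-AB with MDM-C, and a the share of discordant cases in which the reference sides with a given board. With pe held at 0.24, that board's reference kappa is k + a(1 − k). The discordant share is (1 − k) × 0.76.

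| k | Discordant share | Of 600 | a = 0 | a = 0.25 | a = 0.5 |
|---|---|---|---|---|---|
| 0.40 | 0.456 | 274 | 0.40 | 0.55 | 0.70 |
| 0.50 | 0.380 | 228 | 0.50 | 0.625 | 0.75 |
| 0.60 | 0.304 | 182 | 0.60 | 0.70 | 0.80 |
| 0.75 | 0.190 | 114 | 0.75 | 0.8125 | 0.875 |
| 0.80 | 0.152 | 91 | 0.80 | 0.85 | 0.90 |

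From k of about 0.75 upward, both kappas reach the target almost whatever the reference decides. If the reference agrees with neither board and its margins shift, the worst case is about 0.74 at k = 0.75 and 0.79 at k = 0.80. Below that the result is open. At k = 0.60 one comparison can fail, at 0.50 only an exactly even split passes both, and at 0.40 both cannot pass.

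**4. Number of reviewed cases.** Discordant-only review in Arm A yields about 91 cases at k = 0.80 or 114 at k = 0.75. Both are well below 240 and 311. If all 1200 patients had both recommendations, the numbers would be 0.152 × 1200 = 182 and 0.190 × 1200 = 228, still below 240.

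**The case against.** The strongest reply is that Planned analysis should not be read alone. If the Study design rule governs, every case gets a reference decision, both kappas can be estimated and 0.75 is attainable. That is correct. A reader might infer that the reference analysis is doomed under any reading, and the documents do not support this. The defect is the contradiction, together with what follows from one of its two sides.

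A reader might also infer that counting concordant cases as agreeing makes success automatic. No section states that rule, and even under it the pass is near-certain only when the MDM-AB/MDM-C kappa is already about 0.75 or more. What stands is that the comparison would then add little once the primary target is met.

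Discordant-only review is not useless either. Planned analysis also gives the reference MDM the task of judging between the boards where they differ, and review of discordant cases serves that task. It does not serve the two kappas.

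A reader might further conclude that cases whose recommendation is never started drop out of the review. Study design gives the timing but does not say that such cases are excluded, so this remains an inference. The use of later information is a declared purpose of the delay, so it is not an error in itself. Only its fit with the T1 sentence needs settling.

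Two cautions on the numbers also stand. The 0.34 applies whole-sample frequencies to a selected subset. The count of 600 assumes ADBoard output in Arm A only, while the primary outcome section speaks of testing all participants' cases for reproducibility. Neither affects the impossibility result, which holds for any frequencies and any number of cases.

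**Conclusion.** The concern holds as a contradiction between Study design and Planned analysis on which cases the reference MDM reviews. Under the Planned analysis rule, kappa ≥ 0.75 in both comparisons is impossible on the reviewed cases, because the agreement shares would have to sum to at least 1.5 and cannot exceed 1. This needs no assumption about frequencies. The 0.34 for an even split rests on pe = 0.24 in the discordant subset. The 91 and 114 cases rest on equal margins at the planned frequencies and on about 600 cases with both recommendations.

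Severity is moderate. The reference kappas are not among the listed primary or secondary outcomes, and the primary kappa of ADBoard with MDM-C is not affected.

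**What to change.** 1. In Planned analysis, replace the discordance trigger by reference review of all cases that have both recommendations. Study design already implies this, since it covers both arms. A lighter alternative is to review all discordant cases plus a random sample of concordant ones, analysed with inverse sampling weights.
2. On that set, estimate kappa(ref,AB), kappa(ref,C) and their paired difference.
3. In discordant cases, report only the split: reference sides with MDM-AB, with MDM-C, or with neither.
4. If only discordant cases are to be reviewed after all, drop the two kappa ≥ 0.75 targets, report the split alone, and amend Study design to match.
5. State which information the reference decision and its analysis rest on, so that the T1 sentence and the later information allowed in Study design agree.

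The cost is mainly wording. Full review asks for no more than Study design already promises. The sampled version reduces the workload but adds a sampling fraction and weights to specify. According to Trial status, recruitment had not started at this version, so the rule could be settled before the first case.

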### System architecture of ADBoard

ADBoard consists of two main technical components: (a) the automatic completion of missing patient information and (b) the automatic treatment recommendation. The purpose and technical implementation of both components are described below.

Structured patient data in tumor protocols can be incomplete, and missing information is often spread across various departments. Examples of missing information are laboratory, radiology, or pathology results, and tumor size or patient status. In the current state, required data must be retrieved individually in a manual and time-consuming fashion. With ADBoard, information (if present) will be automatically extracted using NLP. The process begins with an existing information extraction model, mEx (medical information Extraction platform) [14], specialized for medical text in German. It will be optimized for the use case with historical MDM data from 2011–2021. The information extraction model will be complemented with regular expressions to guarantee high precision. If a parameter cannot be found, the ADBoard should recognize this and check whether a therapy recommendation can still be made at the MDM or if further diagnostics are necessary. Each piece of information automatically extracted and inserted into an empty field will be highlighted as “automatically-inserted data” and appended with its source document and context information. This allows physicians to quickly check the validity of the provided information.

Next, using the complete set of patient data, appropriate treatment options will be recommended. Building on the existing patient health prediction model EffiCare [15], the decision support system will be trained on both structured and unstructured retrospective MDM data. The system will integrate specified clinical guidelines and combine the output of ML and the physicians to form a joint recommendation. The recommendation will be presented together with a confidence score and a justification (explanation), which describes the relevant factors (features) of the decision based on feature importance and Shapley values. Specifically, the corresponding guideline, the agreement with historical MDM decisions (clustering procedure via distance metrics of the feature vectors, such as influential features or cosine distance), and the patient data relevant for decision-making are detailed. Using feedback from MDM physicians, recommendations can be optimized over time according to clinician preference.

#### Onsite and offsite requirements needed to integrate the AI intervention

The AI components will run on a high-performance computing cluster within the hospital infrastructure. The model will be trained on the MDM patient data of the same hospital within the infrastructure, which will be similar to the real test data during the study. We build upon existing proprietary models and technology and integrate the output into the existing MDM dashboard. To do so, a software interface needs to be defined—to send the model results from the backend to the dashboard. The dashboard will then be extended accordingly.

#### Procedure for data acquisition and selection for the AI intervention

The two pretrained AI components run within Charité infrastructure and have access to the necessary patient information across various hospital departments. As the model will not be able to access the real-time data in the hospital information system, the patient data of patients occurring in the next MDM will be automatically collected within an initial step.

#### Procedure for assessing and handling poor quality or unavailable input data

Availability of data and its quality will have a strong influence on the models. Information extraction models might extract false data and thus negatively affect the performance of our models. This will be addressed by providing the source document and the context in which the extracted information occurs. Conversely, if required data are not present in any of the clinical text sources in the hospital, no information can be extracted. This might have an influence on the decision if a patient can be actually discussed in the MDM. It might have an influence on the treatment recommendation, as less information is available, particularly if the missing information is a crucial input parameter. Either way, the recommendation will be provided with a confidence score. If the decision was based on incomplete information, the confidence score would be lower, indicating insecurity of the model.

## Discussion

AI algorithms have been widely tested in medicine, with medical imaging as a well-known area of its application [16]. There remains great potential for AI to be further integrated into other areas of healthcare and medicine, and our study explores the application of AI in liver cancer care. The complexity of liver tumors and their treatment options necessitate the discussion of patients with liver tumors at MDM-C as an integral part of their treatment plan. From our physicians’ experiences, specialist physicians spend a significant amount of time preparing for and attending these meetings. We identified a medical need here and seek to improve the efficiency of this process using a decision algorithm. The literature has several examples of this, with a number of them focusing on breast tumors [17–19]. To our knowledge, this is the first trial to compare the concordance of MDM-C with an AI-based decision algorithm in producing therapy recommendations in participants with liver tumors. When fully developed, the ADBoard algorithm would produce treatment recommendations for cases that can be clearly classified with all the information necessary for decision-making that are not inferior to that of an MDM-C. Reliable recommendations from the ADBoard save physicians time in discussing straightforward cases, which can be funneled to focusing on more complex cases instead. ADBoard will streamline the MDM process further by reducing residents’ administrative workload through automation of form-filling with data directly from the health information system.

Possible limitations of the study are the single-center design, the focus on liver tumor entities, and the inability of the algorithm to consider decision-making factors that may not be included in the hospital information system, such as subjective physical assessments or psychosocial factors.

Potential practical issues in performing the study are external partners in DFKI obtaining the correct permissions and network access to access the Health Data Platform and planning how the therapy recommendations would be displayed during MDMs.

## Trial status

Recruitment has not started. We will begin recruitment in November 2023 and will complete by July 2025.

## Ethics and dissemination

### Research ethics approval

The project was approved by the Ethics Committee of the Charité – Universitätsmedizin Berlin (application number EA4/169/22). Written, informed consent for participation will be obtained from all participants. Participants would potentially join an RCT that assesses the process of MDMs, and this would be explained clearly to them during the process of obtaining informed consent. The model consent form and participation information materials in the German language are available from the corresponding author on request.

### Data management

A data protection concept was developed under the advice of the Clinical Trial Office Charité, based on the European Union General Data Protection Regulation.

The full dataset will be accessible to the physicians. The pseudonymized dataset will be accessible to research team members who require it for analysis purposes. It will be password-protected and stored on a server within the study institution. The PI and other study investigators authorized by the PI will safeguard the final trial dataset. Any data required to support the protocol can be supplied on reasonable request and in line with the data security laws of Berlin, Germany.

Identifiable information about potential and enrolled participants will be collected in REDCap and stored on a local server within the institution. The participants’ data will be pseudonymized and the researchers will work with the pseudonymized data. The participants’ data will be kept for up to 10 years after the end of the trial and then deleted.

The various components for data processing and decision-making will be deployed on a Linux server within the study institution. DFKI researchers will develop the models on this server to ensure that no data will leave the study institution.

To ensure that all collected health data are unidentifiable, the research-related paper forms (e.g., consent forms) and electronic data will be stored physically separately from participants’ medical records. The paper forms are stored in a lockable room in a lockable cupboard accessible only by the principal investigator (PI) and persons authorized by him. The PI is responsible for storing and managing the identification list. The password-protected access authorization to the servers used is exclusively granted by the PI.

### Auditing

The Trial Management Committee and Experimental Surgery Berlin, a research group of the Charité independent of the study research team, meet every 2 months to review trial conduct.

### Plan for dissemination

We intend to disseminate the results of the study to the general medical community via publication in medical journals, regardless of the magnitude or direction of effect. The trial register at ClinicalTrials.gov will be updated with the results as they become available. At the time of manuscript submission, there are no known restrictions to the right to publish study results on any members of the research team.

Subject to German data security law, the full protocol, participant-level dataset, and statistical code are available from the corresponding author on reasonable request, for cooperation purposes only.

### Protocol amendments

Any protocol amendments that may affect the way the study is conducted or its participants, such as changes in study objectives or design, inclusion or exclusion criteria, or outcomes evaluated, will require a formal amendment to the protocol. All members of the research group and the ethics committee must agree upon such amendments before their implementation. Administrative changes that do not have a similar effect are considered minor amendments and will be documented in an addendum to the protocol. All approved protocol amendments will be clearly stated in trial reports.

